#### *Determinants not addressed by the implementation intervention*

The implementation intervention aims to address a variety of determinants identified in previous work. There were some determinants which could not be addressed within this intervention, generally because additional resources would be required. These include:

• Use of health care assistants/receptionists to weigh patients

• Patients are only weighed as part of their routine care. Therefore, some patients are not weighed on a regular basis.

• A trained specialist individual within primary care who can conduct everything (weighing, advice, assess motivation, offer referral).

• Local referral policies may restrict the range of patients who can be referred to specialist care.

• Dietitian run clinic in GP surgery.

• Running a group service at the GP surgery which provides weekly advice/support.

The teams in the control group will receive no interventions. After the trial has ended, they will receive feedback about their own performance in comparison with the performance of others in the study, in relation to the guideline recommendations. They will receive no other interventions.

If the intervention is successful, teams in the control group will be offered a compact disc containing all the materials and resources used within the intervention teams.

### Outcomes

#### *Primary outcome*

The primary outcome measure relates to recommendation 3 (Table 1), the proportion of overweight or obese patients to whom the health professional has offered a weight loss intervention within the study period. The patient population is defined as all patients with a BMI measurement of 25 kg/m^2^ or higher recorded in their medical notes at the time of the centre randomisation.

#### *Secondary outcomes*

We will collect data from each practice on:

• The proportion of patients with a BMI or waist circumference measurement recorded within the study period (recommendation 1);

• the proportion of patients with a record of lifestyle assessment (recommendation 2);

• referral to external weight loss services (recommendation 4);

• the proportion of overweight/obese patients who changed weight (lost or gained 1 kg) during the study period;

• the mean weight change over the same period.

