**Methods/Design:**

The study is a cluster randomised controlled trial. Primary care teams will be recruited from the East Midlands of England, and randomised into two study arms: 1) the study group, in which primary care teams are offered a set of tailored interventions to help implement the NICE guidelines for overweight and obesity; or 2) the control group in which primary care teams continue to practice usual care. The primary outcome is the proportion of overweight or obese patients for whom the primary care team adheres to the NICE guidelines. Secondary outcomes include the proportion of patients with a record of lifestyle assessment, referral to external weight loss services, the proportion of obese patients who lose weight during the intervention period, and the mean weight change over the same period.

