In order for a weight loss intervention to be successful the patient needs to be ready and willing to make changes to their lifestyle. If the patient is not ready and willing to do so, it is likely the intervention will fail. The NICE guidelines recommend that health care professionals assess a patient’s lifestyle, co-morbidities and willingness to change. This can be difficult to assess in a short consultation. The intervention will explain how to assess whether a patient is ready to make changes to their lifestyle. Health care professionals will also be provided with questionnaires to assess motivation and that can be used as a discussion point with patients.

The intervention will also provide health care professionals with resources that can be used to increase a patient’s motivation, and suggest appropriate times to use them within the consultation. The resources will demonstrate the benefit of a modest weight loss (5 or 10% of body weight) for the patient.

##### 

**Recommendation 3: Management of overweight and obesity** Determinants addressed:

• Lack of prescriptive information

• Lack of knowledge

Many patients interviewed during our investigation of determinants felt that they were aware of the concept of healthy eating, and the need to reduce their calorie intake to lose weight, but they felt more prescriptive advice would be of benefit. They felt that the advice provided by commercial slimming clubs on portion sizes and guidance on a more prescriptive diet would be beneficial. The intervention will provide health care professionals with a prescriptive weight loss plan that can be delivered to patients within primary care. The ‘Weight loss you can see’ information booklet provides patients with visible pictures of portion sizes for every day foods. The booklet provides patients with a prescriptive energy deficit diet. The energy level prescribed for a patient will be based on an estimate of their initial maintenance energy needs minus 600 kcal/day [1]. Health care professionals will be provided with training to calculate energy requirements, and the required portions of carbohydrates, vegetable, protein and dairy foods [28].

Health care professionals felt that they did not always have sufficient knowledge or skill to advise patients on changes to their diet. The intervention will also provide health care professionals with a summary of the NICE guidelines for diet and exercise.

##### 

Recommendation 4: Referral

Determinants addressed:

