### Measurement procedures

In each general practice, measurements of performance by participating primary care teams (GPs and practice nurses) will be performed at baseline and at follow-up after up to 9 months (the study period).

The following measurement methods will be used: record audit for primary and secondary outcome measures, and interviews and questionnaires for primary care teams to collect information on the process of the study.

Specific measures will include:

1. Data relating to the primary and secondary outcome measures will be obtained from the electronic medical records that are routinely collected in each general practice. We have developed bespoke data extraction software for use in a pilot study. This software will be adapted to ensure capture of all the relevant data from records. All adults in each practice are included, and full data protection procedures will be followed. The software will identify those patients with a recorded BMI of 25 kg/m^2^ or over, and the recorded management of those patients. Baseline and follow-up data will be collected in one data extraction at the end of the intervention.

2. An interview will be undertaken with a primary care team member to identify the numbers of registered patients, patient demography, performance in the QOF and procedures for managing obesity.

3. To assess the tailoring of the intervention, we will record notes on the delivery of the implementation interventions to each team, how it is perceived and if and how it is adapted. We will also interview a member of the primary care team to explore their experiences of the interventions.

4. The practice obesity lead will be asked to complete a self-report questionnaire to the obesity lead of the participating primary care team to identify any deviations from the interventions and any adaptations that were necessary, and why.

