### Statistical methods

Using an intention-to-treat approach, the primary analyses will use generalised estimating equations that assume the outcome has a binomial distribution, include a term to account for the practice-level clustering, and use a logit link function to compare the proportion of overweight and obese patients that have been offered a weight loss intervention between the two arms. The secondary outcomes will be analysed using similar methods, with appropriate distributions and link functions selected. Baseline is defined as the last value obtained within 1 year prior to randomisation. Missing values of quantitative endpoints will not be imputed.

A detailed Statistical Analysis Plan will be produced prior to collection of the data and the database lock. Data collected from electronic records will be transferred to a statistical package for analysis. A Consolidated Standards of Reporting Trials (CONSORT) diagram showing the progress of clusters and patients through phases of the trial will be produced [32]. Descriptive characteristics of the centres and their patients at baseline and follow-up will be summarized by treatment arm, using mean (standard deviation) or median (interquartile range) for continuous variables as appropriate, and count (percentage) for categorical variables.

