### Sample size

It is assumed that, in the control arm, the adherence will be 46%. These estimates are based on a local pilot study of management of obesity in primary care completed in 2010 to 2011, and were measured at the team level and so are an approximation [14]. The aim of the study is to detect an increase to 60% adherence in the intervention arm with 80% power, using a two-sided test with alpha of 0.05. The intraclass correlation coefficient is assumed to be 0.05.

We determined the number of clusters per treatment using these values and with various numbers of clusters and cluster sizes (Table 4) (R-package CRTsize) [33].

**Table 4 T4:** Study power depending on number of clusters and average cluster size

Average cluster size (M)	> 1,130	163-212	213-309	310-568	569-3,464	> 3,464	> 287
Power (1-β)	0.80	0.80	0.81	0.82	0.83	0.84	0.85
Number of clusters (N)	12	13					14

As the average number of overweight patients per centre with baseline data is likely to be larger than about 500, it was deemed adequate to choose a total sample size of 28 primary care teams, which would allow adequate power even in the case of a drop out of up to four teams.

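### The secondary weight-change outcome pools 1 kg losses with 1 kg gains, so taken literally it cannot separate benefit from harm, and it conflicts with the abstract.

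*Protocol article*

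**What the plan says.** The Secondary outcomes section lists "the proportion of overweight/obese patients who changed weight (lost or gained 1 kg) during the study period" and, in the next bullet, "the mean weight change over the same period".

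The abstract (Methods/Design) gives the same pair as "the proportion of obese patients who lose weight during the intervention period, and the mean weight change over the same period".

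The direction the programme aims for is not in doubt. Under The recommendations, the article describes the motivational materials for patients: "The resources will demonstrate the benefit of a modest weight loss (5 or 10% of body weight) for the patient".

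On analysis, Statistical methods says "The secondary outcomes will be analysed using similar methods, with appropriate distributions and link functions selected". It does not say whether losses and gains are counted apart, or which of the two definitions applies.

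**The concern.** The intervention is meant to bring weight down, yet the event in the Secondary outcomes section is met equally by a patient who loses 1 kg and one who gains 1 kg. A patient whom the programme turns from a gainer into a loser stays in the numerator. A difference between arms in this proportion would therefore have no clear meaning, and no difference could hide a real shift in weight.

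The abstract adds a second problem. Its outcome is loss only, so the article holds two incompatible definitions of what is evidently the same item. Readers of the results could not tell which one had been specified in advance. This is the only yes/no outcome on patients' weight that the article lists.

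**Working it through.** **Step 1. The two definitions side by side.**

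| Feature | Secondary outcomes section | Abstract |
|---|---|---|
| Direction | loss or gain | loss only |
| Threshold | 1 kg | none stated |
| Population | overweight and obese | obese |
| Period label | study period | intervention period |
| Companion outcome | mean weight change | mean weight change |

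The shared companion outcome and the order of listing show that these are two versions of one item. Both are current text. The period labels may mean the same interval; the other three differences are of substance.

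**Step 2. Is there a figure to reproduce?** No. The article gives no expected rate, SD, effect or power for this outcome. The sample size section concerns the primary outcome only. What follows is an illustration on stated assumptions.

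**Step 3. Set-up.** Assumptions: weight change D is normal with mean μ and SD σ; the control mean is 0; σ is 3 to 6 kg; and the 1 kg threshold means at least 1 kg. With Φ the standard normal distribution function:

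- P(loss) = P(D ≤ −1) = Φ((−1 − μ)/σ)
- P(gain) = P(D ≥ 1) = 1 − Φ((1 − μ)/σ)
- P(pooled) = P(loss) + P(gain)

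Replacing μ by −μ swaps P(loss) and P(gain) and leaves the sum unchanged. A mean loss and an equal mean gain therefore give the same pooled proportion at every σ.

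**Step 4. Numbers at σ = 5.**

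- μ = 0: loss Φ(−0.2) = 42.1%; gain 42.1%; pooled 84.1% (from unrounded values).
- μ = −1: loss Φ(0) = 50.0%; gain 1 − Φ(0.4) = 34.5%; pooled 84.5%.
- μ = +1: loss 34.5%; gain 50.0%; pooled 84.5%.

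**Step 5. A true mean loss of 1 kg across the range of σ.** Shifts are taken from unrounded values.

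| σ (kg) | Pooled, μ = 0 | Pooled, μ = −1 | Shift (points) | Loss ≥ 1 kg, μ = 0 | Loss ≥ 1 kg, μ = −1 | Shift (points) |
|---|---|---|---|---|---|---|
| 3 | 73.9% | 75.2% | 1.36 | 36.9% | 50.0% | 13.1 |
| 4 | 80.3% | 80.9% | 0.60 | 40.1% | 50.0% | 9.9 |
| 5 | 84.1% | 84.5% | 0.31 | 42.1% | 50.0% | 7.9 |
| 6 | 86.8% | 86.9% | 0.18 | 43.4% | 50.0% | 6.6 |

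The pooled proportion moves by 0.2 to 1.4 points and the loss-only proportion by 6.6 to 13.1 points.

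**Step 6. The sign depends on where the control arm starts.** At σ = 5, suppose control patients gain 1 kg on average and the intervention holds the mean at 0. The pooled proportion then falls from 84.5% to 84.1%, although patients have benefited. In Step 4 a benefit of the same size, from 0 to −1 kg, made it rise.

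**The case against.** The wording can be read another way. The bullets follow a statement of what data will be collected, and the parenthesis may mean that the 1 kg threshold applies in each direction, with patients classed as having lost or gained. The mean-change bullet and the abstract both suggest that the authors cared about direction. How categories are coded is normally settled in the analysis plan, which the article promises before data collection and which is not shown here.

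Part of this stands. The two-category reading is possible, so the interpretability problem holds for the literal wording and not necessarily for what was intended. But the text names one proportion and nowhere says that losses and gains are compared separately. An analysis plan would also not remove the disagreement between abstract and outcomes section, which is stated text and not omitted detail.

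A reader might go further and infer any of the following, none of which the document supports:

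- *The trial cannot tell whether patients' weight improved.* It can: mean weight change is listed as a secondary outcome and is signed.
- *The main result is compromised.* The primary outcome is the offer of a weight loss intervention, and neither it nor the sample size depends on this item.
- *The pooled outcome is near its ceiling.* Under the assumptions above, its baseline is 74% to 87%.
- *Two definitions mean the choice will be made after seeing the data.* They leave room for that, but a plan fixed before data collection could close it.

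**Conclusion.** The point holds as a moderate defect in one secondary outcome. Taken literally, the outcome in the Secondary outcomes section pools opposite results and cannot distinguish benefit from harm. It also disagrees with the abstract on direction, threshold and population. Confidence is high on the mismatch, which is plain from the text. The loss of interpretability depends on the literal, pooled reading.

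The size is illustrative only. The shifts of 0.2 to 1.4 points (pooled) against 6.6 to 13.1 points (loss only) rest on assumed normality, a control mean of 0 and SDs of 3 to 6 kg, none of which the article gives. That a mean loss and an equal mean gain score the same needs only a symmetric distribution around the mean; the SD affects only how insensitive the outcome is.

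**What to change.** Define the outcome as the proportion of patients who lose at least 1 kg, and report the proportion who gain at least 1 kg separately. Alternatively, use a single ordered outcome with the levels lost, stable and gained. State one direction, threshold, population and period, and use them identically in the abstract and the Secondary outcomes section. Carry the same definition into the analysis plan before the data are extracted.

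The cost is a change of wording. No new data are needed, because the weights required for the mean-change outcome, taken from the same record extraction, are enough to classify each patient.

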### Measurement procedures

In each general practice, measurements of performance by participating primary care teams (GPs and practice nurses) will be performed at baseline and at follow-up after up to 9 months (the study period).

The following measurement methods will be used: record audit for primary and secondary outcome measures, and interviews and questionnaires for primary care teams to collect information on the process of the study.

Specific measures will include:

1. Data relating to the primary and secondary outcome measures will be obtained from the electronic medical records that are routinely collected in each general practice. We have developed bespoke data extraction software for use in a pilot study. This software will be adapted to ensure capture of all the relevant data from records. All adults in each practice are included, and full data protection procedures will be followed. The software will identify those patients with a recorded BMI of 25 kg/m^2^ or over, and the recorded management of those patients. Baseline and follow-up data will be collected in one data extraction at the end of the intervention.

2. An interview will be undertaken with a primary care team member to identify the numbers of registered patients, patient demography, performance in the QOF and procedures for managing obesity.

3. To assess the tailoring of the intervention, we will record notes on the delivery of the implementation interventions to each team, how it is perceived and if and how it is adapted. We will also interview a member of the primary care team to explore their experiences of the interventions.

4. The practice obesity lead will be asked to complete a self-report questionnaire to the obesity lead of the participating primary care team to identify any deviations from the interventions and any adaptations that were necessary, and why.

### Process evaluation

A detailed protocol for a process evaluation has been developed as is being reported separately [31]. In accordance with this protocol, we aim to examine the fidelity of the planned intervention strategy and how this relates to the effectiveness of the implementation programme, and to identify possible mechanisms underlying effectiveness (or lack of it) on primary and secondary outcomes.

### Recruitment

All primary care teams in the East Midlands of England will be invited to participate in the study. The area includes the following CCGs: Leicester City CCG, East Leicester & Rutland CCG, West Leicestershire CCG, NHS Southern Derbyshire CCG, North Derbyshire CCG, NHS Lincolnshire East CCG, Lincolnshire West CCG, North East Lincolnshire CCG, North Lincolnshire CCG, Mansfield and Ashfield CCG, Nottingham North & East CCG, Nottingham West CCG, Rushcliffe CCG, NHS Nottingham City CCG, Newark & Sherwood CCG, NHS Corby CCG and Nene CCG. Letters of invitation, with information about the study, will be sent to all the primary care teams in these CCGs.

### Randomisation

Randomisation to the two treatment groups will take place at the level of the practice team; however, we are undertaking the primary analysis at the patient level, and therefore this is a cluster randomised trial.

The randomisation will be stratified by list size (<6000, ≥6000) and deprivation (<20,≥20 practice Index of Multiple Deprivation scores 2010), where the cut-off points are related to the median of each of variable of all regions in England [27].

Centres will apply for randomisation sequentially. To avoid larger imbalances between the four strata (to mimic the underlying distribution of GP practices in England), the following restriction will be implemented: none of the 4 strata shall contain more than 10 practices, and the maximum of 10 practices is only allowed if all other strata contain at least 4 practices, otherwise the maximum should be 8. The randomisation will be performed independently from the trial office by the Leicester Clinical Trials Unit.

### Blinding

Participant teams cannot be blinded to whether or not they are receiving an intervention. Data collection will use a standard electronic system and, to minimise bias, all data will be collected using full anonymisation using a standardized data query.

### Statistical methods

Using an intention-to-treat approach, the primary analyses will use generalised estimating equations that assume the outcome has a binomial distribution, include a term to account for the practice-level clustering, and use a logit link function to compare the proportion of overweight and obese patients that have been offered a weight loss intervention between the two arms. The secondary outcomes will be analysed using similar methods, with appropriate distributions and link functions selected. Baseline is defined as the last value obtained within 1 year prior to randomisation. Missing values of quantitative endpoints will not be imputed.

A detailed Statistical Analysis Plan will be produced prior to collection of the data and the database lock. Data collected from electronic records will be transferred to a statistical package for analysis. A Consolidated Standards of Reporting Trials (CONSORT) diagram showing the progress of clusters and patients through phases of the trial will be produced [32]. Descriptive characteristics of the centres and their patients at baseline and follow-up will be summarized by treatment arm, using mean (standard deviation) or median (interquartile range) for continuous variables as appropriate, and count (percentage) for categorical variables.

### Sample size

It is assumed that, in the control arm, the adherence will be 46%. These estimates are based on a local pilot study of management of obesity in primary care completed in 2010 to 2011, and were measured at the team level and so are an approximation [14]. The aim of the study is to detect an increase to 60% adherence in the intervention arm with 80% power, using a two-sided test with alpha of 0.05. The intraclass correlation coefficient is assumed to be 0.05.

We determined the number of clusters per treatment using these values and with various numbers of clusters and cluster sizes (Table 4) (R-package CRTsize) [33].

**Table 4 T4:** Study power depending on number of clusters and average cluster size

Average cluster size (M)	> 1,130	163-212	213-309	310-568	569-3,464	> 3,464	> 287
Power (1-β)	0.80	0.80	0.81	0.82	0.83	0.84	0.85
Number of clusters (N)	12	13					14

As the average number of overweight patients per centre with baseline data is likely to be larger than about 500, it was deemed adequate to choose a total sample size of 28 primary care teams, which would allow adequate power even in the case of a drop out of up to four teams.

